#### Usual care

Patients allocated to the control group will receive pre- and postoperative care as usual according to protocols from their hospital or clinic. All types of care as usual are included. According to the guidelines of the Dutch Orthopaedic Association (NOV), usual care for patients eligible for knee arthroplasty is usually limited to surgical placement of an implant, supplemented by 1) a pre-surgery evaluation by the surgeon and/or physician assistant, 2) pharmaceutical treatment, such as antibiotics or pain relieve medication, and 3) post-surgery clinical check-ups, mainly targeted at wound healing and implant position. This usual care is covered in the Dutch healthcare insurance. Depending on the patient and his/her healthcare insurance, this can be supplemented by physical rehabilitation. Moreover, participants will receive access to eHealth from care as usual. This can consist of an app from the hospital or clinic (such as the Patient Journey App) or a website, depending on the patient’s hospital or clinic. The usual care apps mainly consists of information such as appointment dates, contact information, wound healing information and sometimes rehabilitation exercises. The website shows similar information. For the sake of clarity, the usual care apps and website do not focus on postoperative return to daily activities including work and sports.

### Blinding

Patients will be blinded as both groups receive a form of eHealth, however with a different dose delivered. It will be impossible, however, to blind the researchers, health care providers and case-managers during the data collection, as they will be in contact with patients allocated to the intervention group. After data collection, the data will be pseudonymized and data will be blinded for the researchers during the analyses.

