**Methods:**

The intervention will be tested in a multicentre randomized controlled trial with eleven participating Dutch medical centers (i.e., hospitals and clinics). Working patients on the waiting-list for a total- or unicompartmental knee arthroplasty with the intention to return to work after surgery will be included. After pre-stratification on medical centre with or without eHealth as usual care, operation procedure (total- or unicompartmental knee arthroplasty) and recovery expectations regarding return to work, randomization will take place at the patient-level. A minimum of 138 patients will be included in both the intervention and control group, 276 in total. The control group will receive usual care. On top of care as usual, patients in the intervention group will receive an intervention consisting of three components: 1) a personalized eHealth intervention called ikHerstel (‘I Recover’) including an activity tracker, 2) goal setting using goal attainment scaling to improve rehabilitation and 3) a referral to a case-manager. Our main outcome is quality of life, based on patient-reported physical functioning (using PROMIS-PF). (Cost-)effectiveness will be assessed from a healthcare and societal perspective. Data collection has been started in 2020 and is expected to finish in 2024.

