### Randomization and allocation

Included patients will complete a first (baseline) questionnaire approximately eight weeks before surgery. Thereafter, randomization will be performed at the patient level. Randomization will be performed in a 1:1 ratio using computer-based randomization lists in Excel, developed by an independent statistician of the Epidemiology and Biostatistics department of Amsterdam UMC. Randomization will be pre-stratified by medical centre (with or without eHealth as usual care), operation procedure (total- or unicompartmental knee arthroplasty) and recovery expectations regarding return to work [25], either positive: “I expect to be fully back at work earlier than the average knee arthroplasty patient” or negative: “I expect to be fully back at work later than the average knee arthroplasty patient”. Only for the randomization lists for medical centres that do not have eHealth as usual care, block randomization will be used. The allocation sequence is predetermined by the statistician and cannot be altered by the researchers. The randomization will follow the order of receiving the patient’s digital baseline questionnaire. Patients will be blinded to the randomization to either the control- or the intervention group.

After allocation, each patient will receive an e-mail containing instructions and a link and log-in details to either the ikHerstel app or to the eHealth from their own hospital or clinic (as explained below in the intervention paragraph). The research team will inform the medical team of the corresponding centre and, if a patient is allocated to the intervention group, the patient’s case-manager. If any patient refuses or wishes to withdraw from the study, either during the inclusion period or during the study period, they will continue to receive care as usual only.

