
#### Component 2 – goal setting using goal attainment scaling

The second component involves patient-specific participation goal attainment scaling (GAS). GAS is a valid and reliable tool for facilitating patient-centred rehabilitation care, and has been used for setting patient-centred goals during postoperative rehabilitation [37]. In this way, improvement towards these individual goals and activities can be easily assessed, while potential problems during the rehabilitation can be identified.

During their appointment with their case-manager (component 3), patients will define a specific GAS goal for their post-surgical rehabilitation. This goal has to be related to their work-activities and thus return to work, such as walking stairs at work or lifting boxes during the workday, given that defining such goals have shown to be effective for patient satisfaction regarding their recovery [36]. The case-manager will collaborate with the researchers to validate the patient’s GAS goal. Patients are stimulated to discuss their GAS goal with their physiotherapist in order to achieve their GAS goal and are also stimulated to discuss their goal with their occupational physician, family and friends.

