### Strengths and limitations

This integrated care program is based on extensive preliminary research, including our systematic review on transmural care, focus groups assessing the experiences and wishes of knee arthroplasty patients, earlier research on the ikHerstel app in other patient populations (i.e. gynaecological and abdominal surgery patients), our Delphi study [27] in which we used expert input to develop an algorithm to tailor the eHealth app to knee arthroplasty patients and our studies showing the effectiveness of GAS among this patient group. In these studies, our care program has been critically evaluated and adapted with the help of the involved stakeholders. Another major strength of this integrated care program is the innovative tailored ikHerstel app with the possibility to alter the recommendations for each unique patient, providing more encouragement and relevance to the patient. Furthermore, recovery recommendations will be provided during the first twelve months after surgery, the period during which work participation has shown to occur [13]. And, the nature of our eHealth intervention allows for patients to receive remote care, which has become more relevant in the past years with limitations to travel and visit health care facilities due to the COVID pandemic.

Using PROMIS short forms as primary outcome measurement instrument, we use a form of tailored testing. PROMIS has proven effective as a reliable and valid measurement to assess participation using adaptive testing, in which the selection of items presented to the patient are based on the patient’s own response [42]. This is important to be able to compare the outcomes of various patients with different needs. Additionally, the access to eHealth form care as usual for the control group enables us to blind the patients, leaving them unknown to which group they are allocated. Last, due to the wide diversity of participating hospitals and clinics (academic, teaching, nonteaching, rural and urban), the generalizability of this study will probably be high and will provide a heterogeneous sample of included patients.

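### The protocol states that patients are blinded, but the arms it describes differ in kind, and possible reporting bias in the self-reported primary outcome is missing from the limitations

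*Protocol article*

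**What the plan says.** The protocol article claims patient blinding in three places.

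- Randomization and allocation: "Patients will be blinded to the randomization to either the control- or the intervention group".
- Blinding: "Patients will be blinded as both groups receive a form of eHealth, however with a different dose delivered".
- Strengths and limitations: giving controls access to usual-care eHealth "enables us to blind the patients, leaving them unknown to which group they are allocated".

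The Blinding section accepts that researchers, care providers and case-managers cannot be blinded during data collection. It says the data will be blinded for the researchers at analysis. The limitations text discusses only unblinded health professionals, and offers as reassurance that they do not collect the data.

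On what the arms receive, the abstract says: "On top of care as usual, patients in the intervention group will receive an intervention consisting of three components". For the other arm it says: "The control group will receive usual care".

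**The concern.** Blinding of patients requires that they cannot tell the two regimens apart. Having some form of eHealth in both arms does not achieve that when one arm also has a personal appointment, a goal-setting session and a wearable device that the other lacks.

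This matters because the patient is the assessor of the primary outcome. The patient rates the functioning level for each chosen activity and states the day on which it was reached. If patients' expectations depend on the care they know they are getting, their ratings and dates may depend on it too. A reader who takes the blinding statement at face value would credit the primary hazard ratio with a protection that the described design does not provide. The limitations text would not correct that impression.

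**Working it through.** No arithmetic applies. The protocol gives no figure for this kind of bias, so the check sets its own sections side by side.

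**1. What each arm receives**

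| Element | Intervention arm | Control arm |
|---|---|---|
| eHealth | ikHerstel app with personal recovery plan and weekly recovery monitor (Component 1) | Own centre's app or website (Usual care) |
| Activity tracker | Worn from two weeks before to six months after surgery; step goals from four weeks after surgery (Component 1) | None described |
| Goal setting | Work-related goal attainment scaling goal (Component 2) | None described |
| Case-manager | Meeting about two to four weeks before surgery (Component 3) | None described |

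Component 2 ties the goal to the personal meeting: "During their appointment with their case-manager (component 3), patients will define a specific GAS goal for their post-surgical rehabilitation".

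**2. Is the eHealth itself similar?** After allocation each patient is sent "log-in details to either the ikHerstel app or to the eHealth from their own hospital or clinic". The Usual care section stresses the contrast in content: "the usual care apps and website do not focus on postoperative return to daily activities including work and sports". So even the one element common to both arms differs in purpose, and not merely in dose. Randomization is also stratified by whether the centre has eHealth as usual care, so the protocol itself recognises that this common element varies between centres.

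**3. Does the protocol's own reasoning reach patients?** Case-managers are said to be impossible to blind because they have contact with intervention patients. Those patients are the other party to that contact. The process evaluation also has intervention patients rate the app, the goal setting and the case-manager appointment at six weeks, while primary-outcome data are still being collected.

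**4. Who determines the primary event?** Under Outcomes, the event is resumption of six of eight self-selected activities, each at least one functioning level above baseline, dated by asking the patient. Under Measurements, this is collected by online questionnaire. No independent assessor is described.

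**5. Do the limitations cover this?** The reassurance offered is that health professionals are not involved in data collection. That argument addresses bias from professionals. It does not address patients who report their own outcome.

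Steps 1 to 3 show that the stated ground cannot support the claim. Steps 4 and 5 show that the claim bears on the primary outcome and that the resulting risk is not disclosed.

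**The case against.** The strongest reply is that blinding patients is close to impossible for a programme built on a case-manager and an app, so its absence is no design error. That stands. The fault lies in the claim, in listing it as a strength and in the missing limitation. No change to randomization, endpoint, sample size or analysis follows.

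A reader might also infer more than the protocol supports:

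- **That patients know they are in the experimental arm.** They will notice what they receive. Whether they know which programme is under test depends on the patient information letter and study information in Appendix 3, which is not shown. Both arms are sent log-in details to some eHealth, so masking to the hypothesis is possible. The protocol does not rest its claim on this.
- **That the bias must favour the intervention.** Expectation plausibly works that way. But the weekly monitor and step goals could also make patients more aware of what they have not resumed, or help them date events more accurately. The net direction is not established.
- **That the weekly monitor gives the intervention arm a different primary-outcome measurement.** The monitor concerns activities chosen from a list of 26. The endpoint uses eight of 29 PROMIS items, collected on the same schedule in both arms. The monitor is not described as a source of endpoint data.
- **That the bias can be sized against the earlier app trials, where resumption came 5–13 days sooner.** Those were gynaecological and abdominal surgery patients. Setting an assumed reporting shift against their results says nothing about the size of bias here.

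**Conclusion.** The patient-blinding statements are wrong as written. The only ground given, eHealth in both arms, does not hide a case-manager meeting, a goal-setting session, a tracker and step goals that the protocol describes for one arm only. Patients are not blinded to the care they receive. At most they may be masked to the hypothesis, on the condition that the information letter supports it.

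Because the primary event and its date are patient-reported, expectation and reporting bias may affect the primary result and the self-reported secondary outcomes. The effect is plausibly in favour of the intervention, but the document settles neither its size nor its direction, so no magnitude is attached.

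The conclusion assumes that controls receive no counterpart to the case-manager, goal setting or tracker from the trial. That is how the arms are described. A control patient who happens to own a tracker would not change it.

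**What to change.** 1. Remove the patient-blinding statements from Randomization and allocation and from Blinding, and take patient blinding out of the strengths.
2. Describe patients as not blinded to the care received or, if the information letter supports it, as masked at most to the study hypothesis.
3. Keep the blinding claim only for the researchers at the analysis stage. State in the Harms section whose blinding its sentence on unblinding refers to.
4. Add to the limitations that the primary outcome and the self-reported secondary outcomes may be subject to expectation and reporting bias, of unknown size.
5. Optionally, add one perceived-allocation question in both arms and report it by arm. Place it in the final 12-month questionnaire. At six weeks it could prime the outcome reports still to come. Answers may partly reflect how well recovery went and should be read with that in mind. Inclusion began in October 2020, so patients who have already completed follow-up will not have answered it.

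Items 1 to 4 are text changes. Their cost is a less favourable risk-of-bias statement. Item 5 costs one question in an existing online questionnaire and would give incomplete data.

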### Sample size calculation

We based our sample size calculation on the effect size from a comparable intervention and patient sample [29], and α = 0.05; Power = 80% and an Intraclass Correlation Coefficient (depicting correlation within surgeons) of 0.010. Using a conservative estimation of the effect size, we expected a hazard ratio (HR) of 1.7 and 50% of the patients to return to activities of daily life by the end of the follow-up period in the group who receive our intervention compared to care as usual. Considering this HR, using a 2-sided log-rank test and incorporating clustering of our study (with an estimated 10 patients per surgeon), we need to observe 220 patients. To take 20% dropout into account, we need to recruit 276 patients (i.e. 138 per arm). Agreements were made with all participating centres in which they committed to recruit a certain number of patients, varying between 20 and 80 patients per participating centre.

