### Intervention

#### Development

The development of the care program under study involved various steps, including a systematic review with meta-analysis [14], focus groups with total knee arthroplasty patients [26], and a Delphi study with orthopaedic surgeons, physiotherapists, occupational physicians and a physician assistant [27] to develop the algorithms for the ikHerstel app.

Our systematic review showed that integrated care programs consisting of one or a combination of: an active referral to a case-manager, a patient tailored rehabilitation program using goal setting and/or eHealth, showed small effects on work- and/or sports participation post-surgery [14]. Moreover, previous studies by our research group showed positive effects on societal participation of integrated care programs with similar intervention elements among other patient populations, such as low back pain patients [28, 29] and gynaecological or abdominal surgery patients [30–32]. For the gynaecological and abdominal surgery patients, an eHealth intervention using the ikHerstel app was developed to support and advise them during their post-operative course. This app was previously found to be effective for returning to daily life activities, where patients in the intervention group returned to daily (work) activities 5–13 days earlier than those in the usual care group [30–32]. Because of the promising effectiveness results of the ikHerstel app, we have further developed this care program according to the wishes and preferences of knee arthroplasty patients with focus groups and an algorithm that was developed in a Delphi study [26, 27]. In the latter study, with an expert panel including orthopaedic surgeons, physiotherapists, occupational physicians and an orthopaedic physician assistant, we have developed uniform and multidisciplinary recommendations for the resumption of daily life activities after knee arthroplasty [27]. The recommendations were implemented in our smartphone ikHerstel app. Moreover, an activity tracker was linked to the ikHerstel app to enhance resumption of physical activity [33–35]. Goal attainment scaling was added to the intervention, given the promising results on satisfaction with occupational and leisure time physical activities among younger knee arthroplasty patients [36, 37].

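### As worded, the sample-size inputs do not give 220 patients: with 50% returning to activities in the intervention group, 220 has about 66% to 72% power, not 80%

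*Protocol article*

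**What the plan says.** The section Sample size calculation gives a full set of inputs and a result. It sets "α = 0.05; Power = 80% and an Intraclass Correlation Coefficient (depicting correlation within surgeons) of 0.010". It states "we expected a hazard ratio (HR) of 1.7" and, in the same sentence, "50% of the patients to return to activities of daily life by the end of the follow-up period in the group who receive our intervention", followed by a trailing comparison with usual care. No second proportion is given. The result is "using a 2-sided log-rank test and incorporating clustering of our study (with an estimated 10 patients per surgeon), we need to observe 220 patients". Allowing for 20% dropout, the recruitment target is 276, or 138 per arm.

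The section Randomization and allocation states 1:1 allocation of individual patients.

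On the source of the effect size, Sample size calculation says "We based our sample size calculation on the effect size from a comparable intervention and patient sample [29]". The Development section cites the same reference among programmes in other patient populations, "such as low back pain patients [28, 29]".

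**The concern.** A log-rank calculation first fixes the number of events. The number of patients then depends on the average event proportion over both arms. Attaching 50% to the better arm puts that average well below 50%, so more patients are needed than if 50% were the usual-care proportion. The stated 220 looks too small for the proportion as it is worded.

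The 276 built on this figure is the trial's headline size, and 80% is its headline power. If the trial does not show a difference, a reader needs to know whether a true hazard ratio of 1.7 had roughly a one-in-six or a one-in-three chance of being missed. The paragraph as written does not allow that to be judged.

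**Working it through.** **Inputs.** From Sample size calculation: two-sided alpha 0.05 (z = 1.960), power 80% (z = 0.842), HR 1.7, intraclass correlation 0.010, 10 patients per surgeon, 50% with the event, 20% dropout. From Randomization and allocation: 1:1 allocation by patient.

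**Assumptions.** Proportional hazards are assumed, to obtain the second group's proportion. The article states neither the formula nor a clustering factor, so two standard log-rank formulas are used, each with and without the usual inflation.

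**Dropout step.** 220 / 0.8 = 275, which becomes 276 for equal arms. This step is consistent.

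**Events required.**
- Schoenfeld: 4 × (1.960 + 0.842)² / (ln 1.7)² = 111.5
- Freedman: (1.960 + 0.842)² × ((1.7 + 1) / (1.7 − 1))² = 116.8

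**Clustering factor, derived.** 1 + (10 − 1) × 0.010 = 1.09.

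**Event proportions under three readings of the 50%.**
- Intervention group (as worded): usual care 1 − 0.5^(1/1.7) = 33.5%, average 41.7%
- Both groups together: average 50%
- Usual-care group: intervention 1 − 0.5^1.7 = 69.2%, average 59.6%

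**Patients required** = events / average proportion × clustering factor. **Power at 220** uses d = 220 × average proportion / factor events. By Schoenfeld it is Φ(√d × ln 1.7 / 2 − 1.960). By Freedman it is Φ(√d × 0.7 / 2.7 − 1.960). In the table, the first figure of each pair is Schoenfeld and the second is Freedman.

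| 50% refers to | Factor | Patients required | Events at 220 | Power at 220 |
|---|---|---|---|---|
| Intervention (as worded) | 1.00 | 267 / 280 | 91.8 | 72% / 70% |
| Intervention (as worded) | 1.09 | 291 / 305 | 84.3 | 68% / 66% |
| Both groups | 1.00 | 223 / 234 | 110.0 | 80% / 78% |
| Both groups | 1.09 | 243 / 255 | 100.9 | 76% / 74% |
| Usual care | 1.00 | 187 / 196 | 131.1 | 86% / 84% |
| Usual care | 1.09 | 204 / 214 | 120.3 | 83% / 81% |

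Example for the first row: 111.5 / 0.4174 = 267. Example for the second: 267.1 × 1.09 = 291.

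**Attempts to recover 220 with the sentence as worded.** An exponential-survival formula gives 277 without inflation and 302 with it. A clustering factor slightly below 1 (0.99, that is 1 minus the intraclass correlation) gives about 265 or more. Only a one-sided test with no inflation (Freedman, 92 events / 0.4174 = 220) lands on the figure, and the section states a two-sided test that allows for clustering.

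**HR detectable with 80% power at 220** = exp(2 × 2.802 / √d), by Schoenfeld, holding the events at the values above:
- 50% in intervention: 1.79 (factor 1.00) or 1.84 (1.09)
- 50% over both groups: 1.71 or 1.75
- 50% in usual care with 1.09: 1.67

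**The case against.** The strongest reply is that the sentence is garbled rather than the number wrong. Its trailing comparison with usual care leaves room for a misplaced phrase, and two other readings come close to 220. If the 50% is the usual-care proportion, Freedman's formula with 1.09 gives 214, and a pooled two-proportion formula gives 202 × 1.09 = 220, although that is not the log-rank test the section names. If the 50% is over both groups, Schoenfeld's formula without inflation gives 223. This stands: a reader might infer that the trial has 68% power and not 80%, and the document does not support so firm a statement. The 68% holds only for the sentence as worded and with the 1.09 inflation.

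It is also fair that the article never states 1.09. It follows from the given correlation and cluster size, and this form of inflation suits randomization by cluster. Here patients are randomized individually, so both arms can occur within one surgeon and the factor is probably conservative. This stands too, but it does not rescue the wording, because with no inflation power is still only 70% to 72%. It also weakens the reading with 50% over both groups: that reading reaches 220 only without inflation, while the section says that clustering was taken into account.

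A condensed article need not print the formula or the event count, and their absence is not held against it. Nor can the description of the hazard ratio as conservative be tested, since the cited study's result is not in the document. Neither is part of this point.

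**Conclusion.** The paragraph is wrong as written: its stated inputs do not yield its stated result. With 50% in the intervention group, every two-sided log-rank variant tried needs about 265 to 305 patients, against 220 stated, and 220 gives about 66% to 72% power. This rests on proportional hazards and equal allocation.

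Whether the trial is short of power cannot be settled from the document. If the 50% belongs to usual care, power at 220 is 81% to 83% with the 1.09 factor. If it is the overall proportion, power is 74% to 80%, depending on formula and clustering factor. Either the sentence misplaces the 50%, or the 80% is overstated, and the article has to say which.

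A minor inconsistency sits beside this. The source of the effect size is called a comparable patient sample in one section and is cited under other patient populations, such as low back pain, in another.

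**What to change.** In Sample size calculation, state which group the 50% refers to and the proportion that the hazard ratio implies in the other group. State also which clustering factor was applied, given that patients and not surgeons are randomized. Then:

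- If the 50% is the usual-care proportion, correct the sentence (about 69% in the intervention group). 220 and 80% stand.
- If it is the intervention proportion, restate the power at 220 as about 66% to 72%, or the hazard ratio detectable with 80% power as about 1.79 to 1.84, according to the clustering factor.
- If it is the overall proportion, restate the power as about 74% to 80%, or the detectable hazard ratio as about 1.71 to 1.75.

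Reconcile the two descriptions of the population behind the cited effect size.

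The cost is the rewording of one paragraph. No extra patients are needed, though the stated power may become less favourable.
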